## Abstract

**Background:**

Many students in Germany do not meet recommended amounts of physical activity. In order to promote physical activity in students, web-based interventions are increasingly implemented. Yet, data on effectiveness of web-based interventions in university students is low. Our study aims at investigating a web-based intervention for students. The intervention is based on the Health Action Process Approach (HAPA), which discriminates between processes of intention formation (motivational processes) and processes of intention implementation (volitional processes). Primary outcome is change in physical activity; secondary outcomes are motivational and volitional variables as proposed by the HAPA as well as quality of life and depressive symptoms.

**Methods:**

A two-armed randomized controlled trial (RCT) of parallel design is conducted. Participants are recruited via the internet platform StudiCare (www.studicare.com). After the baseline assessment (t1), participants are randomized to either intervention group (immediate access to web-based intervention) or control group (access only after follow-up assessment). Four weeks later, post-assessment (t2) is performed in both groups followed by a follow-up assessment (t3) 3 months later. Assessments take place online. Main outcome analyses will follow an intention-to-treat principle by including all randomized participants into the analyses. Outcomes will be analysed using a linear mixed model, assuming data are missing at random. The mixed model will include group, time, and the interaction of group and time as fixed effects and participant and university as random effect.

**Discussion:**

This study is a high-quality RCT with three assessment points and intention-to-treat analysis meeting the state-of-the-art of effectiveness studies. Recruitment covers almost 20 universities in three countries, leading to high external validity. The results of this study will be of great relevance for student health campaigns, as they reflect the effectiveness of self-help interventions for young adults with regard to behaviour change as well as motivational and volitional determinants. From a lifespan perspective, it is important to help students find their way into regular physical activity.

**Trial registration:**

The German clinical trials register (DRKS) DRKS00016889. Registered on 28 February 2019

## Background

Studying is a time of new tasks and stressors [1]. It is a time of performance pressure and lack of time as well as financial and future concerns [2]. Physical activity could help students reducing their stress reactivity [3], and it may serve as a potential health promotion resource for students [4]. Physical activity is a protective factor for the development of chronic medical diseases such as diabetes, cardiovascular disease, and cancer [5, 6]. And it can play an important role in the prevention and treatment of psychiatric diseases such as depression [7, 8]. Several meta-analyses have suggested that the effectiveness of regular exercise in reducing depressive symptoms is comparable to psychotherapeutic and pharmacotherapy treatments [7, 9].

However, many students in Germany do not meet the recommended amounts of physical activity [(cf. [10]): only 27.6% of students are physically active for at least 2.5 h with respect to physical activities making them sweat or breathe harder than normal [11]. Compared to a national study by Germany’s public health institute RKI (Robert Koch Institute) [12], students seem to be even less physically active than young adults in general. Within the RKI sample of young adults, 50% indicated to be physically active for at least 2.5 h a week.

In order to promote physical activity in students, web-based interventions are increasingly being implemented [13]. Web-based interventions are cost-effective [14] and allow for a flexible use in public health settings without spatial, personnel and time constraints [15]. Due to their high internet affinity [16], students are ideally suited as a target group for web-based trainings. The effectiveness of web-based health interventions has been proven for a variety of health and risk behaviours [15]. Meta-analyses show that web-based trainings can increase the level and frequency of physical activity with small to medium effect sizes [13, 17]. Although the effectiveness of web-based physical activity training in the general population is well documented, the data on the effectiveness in university students is low.

Most of the studies investigating the effectiveness of web-based trainings to promote physical activity in students show methodological shortcomings [13]. The most common limitations are the lack of randomization, intention-to-treat analyses, or follow-up measurements [(e.g. [18–21]). One exception is the randomized-controlled trial by Sriramatr and colleagues [22]: medium to large effect sizes of the web-based intervention were found for the change in leisure activities (d = 0.73) and high effect sizes for the daily number of steps (d = 1.41). The effects remained until the follow-up assessment after three months (d = 0.72; d = 1.25). However, the sample of this study only includes female students in Thailand. As the authors point out, culture characteristics may be a restriction for the external validity of the results. Another study investigates college females in the USA: Wadsworth and Hallam [21] find an intervention effect of d = 0.23 with regard to the frequency of moderate activities. Yet, no other measure of physical activity is reported (e.g. duration of physical activity, high intensity activities). Both studies [21, 22] investigate an intervention based on Social Cognitive Theory (SCT [23]). Indeed, most interventions in this field of research are based on SCT [17]. Another important theory of health behaviour change—the Health Action Process Approach (HAPA [24])—has not yet been investigated in web-based physical activity trials in students.

The HAPA goes beyond SCT by emphasizing post-intentional processes. It is based on the assumption that the process of changing a health behaviour includes a pre-intentional (motivational) and a post-intentional (volitional) phase. According to the model, an intention to be physically active is developed if more *positive consequences* (e.g. physical fitness) than *negative consequences* (e.g. risk of injury) are expected and when the person is self-confident to be physically active on a regular basis (*self-efficacy*). Additionally, the person has to be aware of potential health risks (*risk perception*, such as heart disease). Once an intention is formed, the behaviour has to be realized, which is called volitional phase. Volitional competencies according to the HAPA are action planning, coping planning, and action control. Within an *action plan*, a person has to specify, when, where, and how he or she wants to implement the behaviour (e.g. ‘I plan to go cycling, every Tuesday at 6 pm’). As plans can always be challenged by situational barriers (e.g. rainy weather, one’s own bad mood or the cosy couch at home [25]), the person must have effective *coping plans* in order to overcome these barriers and stick to the exercise intention (e.g. social commitment, environment control, see [25]). The post-intentional phase should be accompanied by consecutive action control [26], through which ‘the ongoing behaviour is continuously evaluated with regard to a behavioural standard’ ([24], p.165). Lastly, there are two kinds of self-efficacy that are important for intention implementation: maintenance and recovery self-efficacy [24]. By explicating post-intentional processes, the HAPA extends the scope of other behaviour change models (e.g. [23, 27, 28]). Overall, the HAPA provides a flexible, theoretical framework that can be used to describe, explain and predict changes in health behaviours. It has already been used successfully in numerous health promotion studies, for example to promote physical activity [26], healthy eating [29] or flu vaccine uptake [30]. Yet, no HAPA-based physical activity intervention in students has been evaluated.

Based on the HAPA, we developed a web-based psychological training called ‘InterAKTIV Sport’ (German title). The training consists of several web-based self-help modules targeting at motivational and volitional competences (cf. methods section). It aims at promoting exercise behaviour as a subset of physical activity. Physical activity is defined as any (physical) activity that requires energy and is caused by the skeletal muscles [10]. Exercise, on the other hand, covers only those physical activities that are structured, planned and repetitive with the goal of improving or maintaining physical fitness [10]. The intervention focuses concisely on exercise, as exercise is supposed to be more tangible for young adults than “physical activity” in general. Many students are familiar with exercise groups and clubs from their adolescence, but often they lost their relatedness when transiting into student life [31].

The study aims at investigating the effects of the web-based HAPA intervention on physical activity in students (primary outcome). We expect that participants of the intervention group will be more physically active than a waitlist control group at post-intervention and 3 months follow-up. Additionally, we investigate the effects of the intervention on motivational and volitional variables proposed by the HAPA model (secondary outcomes). Quality of life and depressive symptoms are investigated with an explorative approach.

## Methods

### Design

A two-armed randomized controlled trial (RCT) of parallel design is conducted in order to investigate the research questions. Participants are recruited via the internet platform StudiCare (www.studicare.com). All students registering for the study and giving informed consent have access to the baseline assessment (t1). Individuals fulfilling inclusion criteria (student status, older than 18 years, exercising less than three times a week) are randomized to either the intervention group or the control group. There are no further exclusion criteria in order to enable as many students as possible to engage in the training and to achieve a high external validity. Participants in the intervention condition will immediately receive access data for the web-based intervention, while participants in the control group do not receive the intervention until follow-up assessment (t3). For the control group access to the web-based intervention is activated after completing the follow-up assessment (t3). After 4 weeks, post-assessment (t2) is performed in both groups followed by a follow-up assessment (t3) 3 months later.

The RCT is conducted in accordance with the CONSORT 2010 Statement [32] and the extension of the CONSORT Statement for pragmatic effectiveness studies [33]. The documentation of the intervention follows the guidelines for implementation and documentation of web-based intervention studies [34]. The study has been approved by the data protection office and the ethics committee of the University of Freiburg (No.: 504/18) and the trial is registered in the German clinical trials register under DRKS00016889. With respect to trial auditing, the Project Management Group ([name], JB) meets weekly over the course of the trial to oversee conduct and progress of recruitment. An independent data monitoring committee is not implemented, as “InterAKTIV Sport” is a low-risk intervention. Deviations from the study protocol will be fully documented and disclosed in further publications. In case of deviations, the protocol in the clinical trial registry will be updated.

### Recruitment

Participants are recruited via the StudiCare homepage (https://www.studicare.com). StudiCare.com is part of an international research and collaboration project that aims at improving students’ health through web-based interventions [35]. Various health-oriented web-based trainings are presented on the StudiCare homepage. All trainings are free-to-use for students who agree to participate in evaluation studies. The StudiCare project comprises a steadily growing network of almost 20 cooperating universities in Germany, Austria, and Switzerland. The universities regularly inform their students via various channels (e.g. e-mail newsletters, press releases, social media posts) about the possibility of participating in online training courses as part of scientific studies. Some universities also refer to the StudiCare offers on their websites. The university cooperation partners are usually the SGM or psychosocial counselling centres, which also recommend the StudiCare training courses directly to students seeking advice. Thereby, over 400,000 students regularly receive information about new studies on StudiCare. For each study, students can access an online registration form. Once the students’ contact details have been received for our study, the study team will send them detailed study information and a link to an informed consent form. The link leads to the homepage of our study where students give their informed consent online before entering the trial. Recruitment started on March 13, 2019, and is expected to end in October 2020. The expected ending date is only approximative, as the pace of recruitment is dependent of the advertising activities at the partner universities of StudiCare and cannot be influenced by the study team.

### Randomization and blinding

An independent researcher of the Methodological Support Centre of the Rehabilitation Research Network Freiburg, who is not elsewhere involved in the study, prepared randomization and allocation of participants in advance. As a means of randomization, an automated computer-based system is implemented (https://www.sealedenvelope.com/) using permuted block randomization with variable block sizes of 4, 6, and 8 (randomly arranged), in a ratio of 1:1. Participants are informed about their assignment to the intervention or control condition. The means for blinding in this study are limited. Still, data analysts will be blinded by creating syntaxes before adding the treatment condition variable to the data set. Any contact between the research team and study participants (e.g. online assessments, e-mail reminders) is standardized for all study participants (IG and CG) and reduced to a minimum.

#### Intervention condition

Following randomization, participants in the intervention group receive access to the web-based training ‘InterAKTIV Sport’. Participants’ access to other exercise programmes (e.g. university sports programme, personal training) is not restricted. ‘InterAKTIV Sport’ consists of an introductory module, four main modules (1: motivation and objectives, 2: concrete planning, 3: barriers management, and 4: action control), and a final module (see Table 1). The components of the training are derived from the HAPA model.

**Table 1 Tab1:** Module of the web-based intervention ‘InterAKTIV Sport’

Module	Topic	Content
Intro	Introduction	- Information about the course of the training - Technical information
1	Motivation and objectives	- Formulating an exercise goal - Reflecting positive and negative consequences of the exercise goals - Intention formation
2	Action planning	- Concrete planning
3	Barrier management	- Identification of situative barriers - Development of strategies to cope with barriers
4	Action control	- Self-monitoring, self-evaluation, self-reinforcement - Coping with lapses into inactivity
Final	Completion	- Review of the intervention

Each module closes with a homework assignment encouraging the implementation of the new skills in daily life. New modules are available on a weekly basis, given that the participant has completed the previous chapter. The introduction and final module can be completed on the same day as the first or last content module. The training lasts for 3 weeks if a participant completes all modules within the recommended timeframe. To enhance adherence [36], participants are sent e-mail reminders after 3, 7, and 10 days when activated modules are not completed. In the last reminder, they are informed that their account will be deactivated within 4 days if they will not login again. Participants’ access to the intervention platform closes with sending the follow-up assessment.

The training was generated with the e-learning software Articulate Storyline 360. It is available on our own server with a pre-installed ILIAS application [37] which we use for enrolment and management of participants. Login on the platform takes place via personal access data and is open all the time. The usability of the intervention was tested in a pilot study [38]. Participants’ feedback resulted in an improved version of the intervention.

#### Control condition

The control group receives the intervention after completing follow-up assessment. Control group participants are told that they will get access to the intervention after the follow-up assessment. No further instruction is given what to do—or not to do—during this time. Participants’ access to other exercise programmes (e.g. university sports programme, personal training) is not restricted. This is equivalent to “treatment as usual” (TAU) in medical efficacy studies. A detailed description of TAU is assessed at post-treatment. Figure 1 shows the study flow.

**Fig. 1 Fig1:**
[figure not shown]
Study flow

### Proposed sample size

The sample size calculation is based on the difference in change in the primary outcome (physical activity) from pre- to post-assessment in both treatment arms (intention-to-treat analyses). Based on previous studies on web-based physical activity interventions in students, mean effect sizes of around d = 0.5 are expected in per-protocol analyses [18, 22, 39]. In order to detect such intervention effects in two-sided significance testing (α = .05) with a power of 80%, a sample size of 128 participants is required. Taking into account an expected study drop-out of about 20%, 160 participants must be included in the study. This sample constitutes the ITT sample. Adjustment for baseline physical activity scores will further improve the power of the primary comparison.

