### Statistical analyses

According to CONSORT statement [32], sample characteristics of both subgroups will be contrasted descriptively in order to detect relevant differences between the two samples. All analyses for the primary and secondary outcomes will be performed with an alpha level of 5% which means that the analyses for secondary analyses will be explorative. Outcome analyses will follow an intention-to-treat principle by including all randomized participants into the analyses. Outcomes will be analysed using a linear mixed model handling missing data under the assumption that data are missing at random. All participants and data points will be included in the mixed model analyses. The mixed model for the primary outcome (physical activity) will include group, time, and the interaction of group and time as fixed effects and participant and university as random effect. Analyses will use restricted maximum likelihood estimation (REML). For repeated measures (time), an autoregressive covariance structure with heterogeneous variances is assumed. Secondary outcomes will be analysed accordingly. We will calculate between-group effect sizes for the outcomes using the post-intervention estimated means and their pooled observed standard deviation. Additional per protocol analyses will include only those participants completing all three assessments (IG and CG) and at least three intervention modules (IG). For the main outcome, potential moderators will be analysed exploratively by including the following variables and all possible interactions in the mixed model: gender, body mass index, depressive symptoms, self-control competence and recruiting season (separate mixed model for each moderator). All analyses will be conducted using IBM SPSS.

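### The 80% power rests on a per-protocol effect size and is not supported for the intention-to-treat primary comparison

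*Protocol article*

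**What the plan says.** The section on the proposed sample size (Methods) ties the calculation to the change in physical activity "from pre- to post-assessment in both treatment arms (intention-to-treat analyses"). Its next sentence gives the effect: "mean effect sizes of around d = 0.5 are expected in per-protocol analyses [18, 22, 39"]. With "two-sided significance testing (α = .05) with a power of 80"%, it concludes that "a sample size of 128 participants is required", and then: "Taking into account an expected study drop-out of about 20%, 160 participants must be included in the study". The 160 are called the ITT sample. The section closes by saying that adjusting for baseline activity will add power, without a figure.

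The section on statistical analyses sets the main analysis: "Outcome analyses will follow an intention-to-treat principle by including all randomized participants into the analyses". It is a linear mixed model that assumes data are missing at random. The per-protocol analysis is additional. It is limited to participants who complete all three assessments and, in the intervention group, at least three modules.

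**The concern.** The effect and the analysis it is meant to power belong to different populations. A per-protocol effect describes people who used the training. The ITT contrast also averages over people allocated to the training who did not use it.

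The drop-out allowance does not bridge the two. It restores the number of observed outcomes but does not lower the effect. The participants who matter are those in the intervention group who answer the assessments but do not complete the modules: they are in the ITT analysis and outside the per-protocol set. The protocol foresees incomplete use, since the intervention section provides reminders for unfinished modules and deactivation of idle accounts. It gives no expected adherence.

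This is the only power statement for the primary test, and the Discussion concedes low power for the moderator analyses only. A non-significant ITT result could be read against an 80% that was never shown for that comparison.

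**Working it through.** **Inputs from the protocol.** Two-sided α = 0.05, power 80%, d = 0.5, N = 128, drop-out 20%, N = 160 (sample-size section); allocation 1:1 (randomization section).

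**Inputs not given, so assumed.** The ITT effect (or the share of assessed intervention participants who use the training) and the baseline-to-post correlation r. The outcome section cites a retest reliability of .80 for the questionnaire, but that is not a correlation over the trial interval.

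**Step 1: reproduce the plan.** A two-sample t-test at d = 0.5 needs 63.77 per arm, so 64 per arm, 128 in all; power at 64 per arm is 80.1%. Inflation: 128 / (1 − 0.20) = 160. Both figures reproduce.

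**Step 2: allow for dilution.** If a share p of the assessed intervention participants has the full effect, the rest have none and the SD is unchanged, then d(ITT) = 0.5 × p. Unadjusted t-test power:

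| p | d(ITT) | 128 observed (64 per arm) | 160 observed (80 per arm) |
|---|---|---|---|
| 1.0 | 0.50 | 80.1% | 88.2% |
| 0.9 | 0.45 | 71.4% | 80.8% |
| 0.8 | 0.40 | 61.2% | 71.0% |
| 0.7 | 0.35 | 50.2% | 59.5% |

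The column for 128 assumes 20% of outcomes missing and, separately, non-use among those still observed. The column for 160 assumes that every outcome is observed.

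**Step 3: smallest effect detectable with 80% power, unadjusted.** d = 0.499 with 128 outcomes and d = 0.446 with 160.

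**Step 4: baseline adjustment, at d = 0.40 with 128 outcomes.** The result depends on the SD used to standardise d.
- On the post-score SD, the effective d is 0.40 / √(1 − r²). Power is 65% at r = 0.3, 74% at r = 0.5, 80% at r = 0.6 and 96% at r = 0.8.
- On the change-score SD, part of the correlation is already used. The adjusted variance is σ²(1 − r²) against 2σ²(1 − r) for change, a ratio of (1 + r)/2, so the effective d is 0.40 / √((1 + r)/2). Power is 79.5% at r = 0.3, 74% at 0.5, 71% at 0.6 and 66% at 0.8.

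The sample-size section speaks of a difference in change but does not say which SD applies.

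**The case against.** The strongest reply is that the protocol does not show a shortfall. It gives no ITT effect and no adherence, so every dilution above is the reviewer's. This stands, and it rules out saying that the trial lacks 80% power.

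A reader might go further and argue that the 20% who drop out gain nothing, so that d falls to 0.40 and power with 128 outcomes to 61%. That counts the same people twice, once as zero effects and once as missing. The 20% refers to lost assessments, and under the missing-at-random model participants without outcomes do not dilute the observed contrast. If everyone observed used the training, d stays near 0.5 and power near 80%. If all 160 are observed and 20% of the intervention group gain nothing, power is 71%. The 61% needs non-use among those observed on top of the drop-out.

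The protocol also claims a gain from baseline adjustment, and on the post-score scale r = 0.6 would fully offset a fall to d = 0.40. This stands as a possibility only: r is not given, the scale of d is not stated, and the model description lists group, time and their interaction as fixed effects with no baseline covariate.

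A reader might also infer that d = 0.5 was picked from favourable evidence, because the Background reports a study said to "find an intervention effect of d = 0.23 with regard to the frequency of moderate activities". The document does not support using that value here. It concerns a single activity measure, not the total activity score used as primary outcome. The study is also reference 21, within the range 18–21 cited for shortcomings ("The most common limitations are the lack of randomization, intention-to-treat analyses, or follow-up measurements"), as is reference 18, one of the sources for 0.5. Reference 22, named as an exception to those shortcomings, reports 0.73 and 1.41, then 0.72 and 1.25 at follow-up, all above 0.5.

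**Conclusion.** The point holds in limited form. The arithmetic is correct; what fails is the match between the effect size and the analysis. The 80% is shown for d = 0.5 with 128 outcomes, and d = 0.5 is described as a per-protocol effect, so it is not shown for the primary ITT test. It is probably optimistic, because any non-use among assessed intervention participants lowers the ITT effect. With 128 outcomes and no adjustment, even d = 0.45 brings power to 71%. With all 160 observed, 80% would hold down to about d = 0.45.

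The true shortfall is unknown. It rests on adherence among those assessed, the number of outcomes observed, r and the scale of d, none of which the document fixes except the expected 20% drop-out.

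It would also be wrong to reassign the 80% to the per-protocol analysis. That set requires all three assessments and at least three modules in the intervention group. With 20% drop-out, any further exclusion for non-use takes it below 128, and its power at d = 0.5 below 80%.

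**What to change.** Keep N = 160 and reword the sample-size section:
- Stop presenting 80% as the power of the ITT comparison, and do not transfer it to the per-protocol analysis.
- State and justify the assumed ITT effect, or the assumed adherence among those assessed from which it follows, and give the resulting power.
- State the assumed baseline-to-post correlation and whether d is standardised on the post-score or the change score. Say how baseline enters the mixed model, so that the claimed gain can be checked.
- Give the smallest ITT effect detectable with 80% power before baseline adjustment: about d = 0.50 with 128 observed outcomes and 0.45 with 160.

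No extra participants and no change to the analysis are needed. The cost is a stated power that will probably be less favourable than 80%.
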